### Objectives

Our primary aim is to determine which 16-week exercise intervention, namely motor control plus isolated lumbar extension exercises (MC+ILEX, arm 1) or free-weight resistance training (arm 2), is more effective in improving disability in patients with predominant nociceptive chronic LBP. Secondary aims are to (1) assess whether changes in multifidus muscle composition mediate improvements in disability; (2) compare the effects of both interventions on multifidus size and quality, lumbar extensor and gluteal strength, hip range of motion (ROM), pain, health-related quality of life, sleep quality, physical activity level, and satisfaction and recovery; (3) explore whether baseline scores on the Lumbar Spinal Instability Questionnaire (LSIQ) and sex/gender act as moderators of treatment response at 16 weeks; and (4) explore participants’ perceptions, mindsets, experience and satisfaction of exercise therapy before and after completing the 16-week interventions.

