### Statistical analysis

For the primary outcome, we will employ linear mixed-effects model for repeated measures over time using ODI as the dependent variable. The model will include effects for group (MC+ILEX vs free-weight resistance training), time (baseline vs 16 weeks) and group by time interaction. LSIQ score (high >9 and low ≤9) will be incorporated as a covariate and an unstructured covariance matrix will be used. Within the mixed model, we will calculate 95% CIs and p values for the two group contrasts, and for changes in ODI score within each group over 16 weeks. We will conduct similar analyses focusing on multifidus muscle composition and lumbar extensor muscle strength as separate dependent variables. To investigate if changes in multifidus muscle composition mediate improvements in disability, path analysis will be conducted to test the following paths: (a) group allocation at baseline (independent variable) → changes in multifidus muscle composition from baseline to 16 weeks (mediator); (b) changes in multifidus muscle composition from baseline to 16 weeks → changes in disability score (eg, ODI) from baseline to 16 weeks (dependent variable); and (c) group allocation at baseline → changes in disability score from baseline to 16 weeks. LSIQ score (high >9 and low ≤9) will be included in the model as an exogenous variable. For paths (b) and (c), disability score at baseline will be included as exogenous variables as well. The direct, indirect and total effects of treatment on the change in multifidus muscle composition and its 95% CI will be calculated based on non-parametric bootstrap. In addition, the mediation percentage is defined as the ratio of the indirect effect to the total effect, thereby quantifying the size of the mediation effect. The significance of the mediation effect will be tested using bootstrap sampling (times=1000). The model fit will be assessed using the following model fit indices: comparative fit index, Tucker-Lewis index and root mean square error of approximation.^102^ To explore if baseline score on the LSIQ can moderate the response to exercise training in chronic LBP at 16 weeks, we will conduct a linear regression model with changes in multifidus muscle composition from baseline to 16 weeks as the dependent variable. The independent variables will include group, LSIQ score (high >9 and low ≤9) and the interaction between group and LSIQ score (high >9 and low ≤9). Multifidus muscle composition at baseline will be adjusted as covariates in the model. Similar analyses will be conducted with changes in ODI score, multifidus size, lumbar extensor strength, pain, sleep and quality of life score from baseline to 16 weeks as the dependent variables, separately. Both complete case analysis and multiple imputation will be conducted to handle missing data. Any participant characteristics identified to be associated with missingness and the outcome will be integrated into the multiple imputation process. This will be accomplished using the fully conditional specification method fitted using predictive mean matching approach. Given the potential for missing data that are not missing at random, we will perform a sensitivity analysis to assess the robustness of our findings under the most unfavourable assumptions about the missing data. In this analysis, if we show that the MC+ILEX group is more effective than the free-weight resistance training exercise group in improving patients’ disability, all missing outcomes at 16 weeks will be imputed with the worst observed outcome in the MC+ILEX group and the best observed outcome in the free-weight resistance training exercise group, and vice versa.

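### The mediation effects are defined on multifidus change, which is the mediator, instead of on ODI change; baseline multifidus fat is also absent from the listed path-model covariates

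*Protocol article*

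**What the plan says.** All of this is in the protocol article.

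- **Aim.** Under Objectives, the first secondary aim is to "assess whether changes in multifidus muscle composition mediate improvements in disability".
- **Paths.** Under Statistical analysis, the first path is "a) group allocation at baseline (independent variable) → changes in multifidus muscle composition from baseline to 16 weeks (mediator"). Path (b) runs from that mediator to "changes in disability score (eg, ODI) from baseline to 16 weeks (dependent variable"). The third path is "c) group allocation at baseline → changes in disability score from baseline to 16 weeks".
- **Effects to be reported.** "The direct, indirect and total effects of treatment on the change in multifidus muscle composition and its 95% CI will be calculated", by non-parametric bootstrap. The mediation percentage is then the indirect effect divided by the total effect.
- **Covariates.** The LSIQ stratum enters the path model. Baseline ODI is added for two paths: "For paths (b) and (c), disability score at baseline will be included as exogenous variables as well". Baseline multifidus composition is listed for none.
- **Moderator regression.** Its first dependent variable is the same multifidus change score, and here the section states: "Multifidus muscle composition at baseline will be adjusted as covariates in the model".

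**The concern.** The paths and the effect definition disagree about which variable is the outcome. A mediation decomposition splits the effect of treatment on the final outcome, here ODI change, into a part that runs through the mediator and a part that does not. The article attaches the decomposition to the mediator itself. No other sentence names the outcome of the direct, indirect and total effects, and the mediation percentage is built on them. Left as it stands, the prespecified quantity for the trial's main mechanistic question is ambiguous and would have to be settled after the event.

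The second matter is smaller. The mediator is a change score, and a change score is usually correlated with its own baseline. Group is randomised but the mediator is not, so the mediator-to-outcome path (b) relies on adjustment for shared causes. Baseline %FSF is an obvious candidate, and the same section already adjusts for it elsewhere.

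**Working it through.** **Plan's own figures.** The article gives no number for the mediation analysis. Its sample size reproduces: d = 0.60, 80% power and two-sided 0.05 give 44.6 by the two-sample t-test, hence 45 per arm and 90 in all; 45/0.85 = 52.9, hence 53 per arm and 106 in all. N = 90 is used below.

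**1. Effect definition**

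Write T for group, ΔM for multifidus change and ΔY for ODI change.

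- Path (a): T → ΔM, coefficient a.
- Path (b): ΔM → ΔY, coefficient b.
- Path (c): T → ΔY, coefficient c, given ΔM.

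| | Outcome ΔY (aim and paths) | Outcome ΔM (literal sentence) |
|---|---|---|
| Direct | c | a |
| Indirect | a × b | 0 (no intermediate variable between T and ΔM) |
| Total | c + a × b | a |
| Mediation percentage | a × b / (c + a × b) | 0 / a = 0 |

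The right-hand column holds for any data set with a non-zero estimate of a.

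**2. Baseline %FSF**

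The article does not give the inputs, so these are assumptions. Baseline and follow-up %FSF (M0, M1) are standardised with correlation r = 0.5, 0.8 or 0.9. a = 0.5 and b = 0.3, so the true indirect effect is 0.5 × 0.3 = 0.15. Baseline %FSF has its own effect g on ODI change of 0, 0.2 or 0.4 (residual SDs of ODI change per SD of baseline %FSF).

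*Path (a).* Group is randomised, so leaving out M0 does not bias a.

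*Path (b).* Within arm:

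- cov(M0, ΔM) = r − 1 = −(1 − r)
- var(ΔM) = (1 − r)² + (1 − r²) = 2(1 − r)
- regression of M0 on ΔM = −(1 − r) / [2(1 − r)] = −0.5, whatever r is

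The unadjusted coefficient therefore estimates b − 0.5g.

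| g | Unadjusted b | Unadjusted a × b (true 0.15) | Unadjusted a × b if true b = 0 |
|---|---|---|---|
| 0 | 0.3 | 0.15 | 0 |
| 0.2 | 0.3 − 0.1 = 0.2 | 0.5 × 0.2 = 0.10 | 0.5 × (−0.1) = −0.05 |
| 0.4 | 0.3 − 0.2 = 0.1 | 0.5 × 0.1 = 0.05 | 0.5 × (−0.2) = −0.10 |

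If g has the opposite sign the bias reverses: 0.5 × 0.4 = 0.20 and 0.5 × 0.5 = 0.25 in place of 0.10 and 0.05.

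A simulation (N = 90, 1,500 replicates per scenario, three values of r) agrees. The unadjusted a × b averaged 0.151 to 0.152 for g = 0, 0.100 to 0.102 for g = 0.2, and 0.046 to 0.053 for g = 0.4. With M0 in both equations it stayed between 0.146 and 0.154. Path (a) averaged about 0.50 throughout. Adjustment cost little precision: at r = 0.8 and g = 0.2 the standard deviation of a × b was 0.095 without and 0.104 with M0.

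**The case against.** **The model itself is right.** The mediation passage opens with the aim, labels the mediator and dependent variable correctly, and plans a bootstrap test of the mediation effect. An analyst who fits the stated paths obtains a × b on ODI change. This stands. A reader might infer that the plan leaves the aim untested; the documents do not support that, because the three paths and the test identify the right quantity. Nor are the literal effects undefined: they are zero, and so uninformative. What remains is a sentence that contradicts its surroundings.

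**The baseline %FSF bias is conditional.** This also stands. The Introduction reports that fatty infiltration goes with greater pain severity and dysfunction, which makes a link plausible, but no figure connects baseline %FSF with ODI change. If there is no such link there is no bias. The full covariate list could also sit in an analysis plan that is not shown. Against that, the article does assign covariates path by path, and its treatment of the same change score differs between two models in one section.

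**Fit indices.** The plan will assess fit by "comparative fit index, Tucker-Lewis index and root mean square error of approximation". A reader might infer that a correct mediation model could be discarded on these. The article states no cut-off and no rule for rejecting the model, so that inference has no basis in the text.

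**Conclusion.** The effect definition is wrong as written. It contradicts the first secondary aim and the article's own path model, and taken literally it fixes the indirect effect and the mediation percentage at zero. This conclusion needs no assumption beyond the three stated paths.

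The absence of baseline %FSF is an inconsistency and a possible source of bias in path (b), not a demonstrated error. The fall from 0.15 to about 0.10 or 0.05 is illustrative. It rests on the assumed standardised values and on equal variance of %FSF at both visits, and its direction depends on the sign of the baseline effect.

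Both matters concern one secondary, mechanistic analysis. The primary ODI comparison and the sample size are untouched, so this ranks below a defect that must be repaired before the trial can answer its main question. It is still worth correcting because mediation is the first secondary aim.

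**What to change.** 1. In the effect sentence, make the change in ODI from baseline to 16 weeks the outcome of the direct, indirect and total effects. Report the indirect effect in ODI points with its bootstrap confidence interval.
2. Add baseline %FSF as a covariate to both the mediator equation and the ODI-change equation, in line with the moderator regression.

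The cost is wording in the protocol and any analysis plan. The Data collection section already schedules all outcomes at baseline and 16 weeks, so no new measurement is needed, and the sample size does not change.

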## Introduction

 Low back pain (LBP) remains the leading cause of disability,^1^ yet effective conservative management strategies are still limited despite decades of research.^2^ Exercise therapy is endorsed in clinical guidelines^3^ and supported by evidence arising from multiple systematic reviews^4^ as a first-line treatment of subacute and chronic non-specific LBP. Exercise is more effective than no intervention in managing chronic LBP^5^; however, the effect sizes for differences between exercise approaches remain modest.^4^ Several factors are likely to contribute to these limited effect sizes, including: (1) the heterogeneity of clinical presentations in LBP,^6^ (2) lack of risk-stratified approaches to enhance treatment selection,^7^ (3) suboptimal exercise dose prescription (dose/intensity are too low),^8^ (4) limited data regarding the influence of paraspinal muscle morphology on clinical outcomes^9^ and (5) clinicians holding unhelpful beliefs about LBP that may hinder appropriate exercise and reduce patient adherence.^10^ The proposed study aligns with international LBP initiatives^11^ and aims to address these gaps by implementing a rigorous clinical approach that integrates best practice recommendations while considering the complex biopsychosocial nature of LBP. An utmost limitation in most previous randomised controlled trials (RCTs) is the delivery of exercise without considering patient phenotype and/or the clinical heterogeneity of the chronic LBP population.^12^ This mismatch between interventions and patient profiles likely contributed to poorer outcomes and reduced effect sizes.^13^ To date, although promising multidimensional risk-stratification tools^14^ and biopsychosocial diagnostic frameworks ^15^ such as the Pain and Disability Drivers Management Model (PDDM)^16^ exist, few have been tested or implemented to guide exercise intervention RCTs.^10 16 17^

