As done in our pilot work,^35^ MC will be combined with ILEX exercise to maximise the stimulus and activation of the lumbar extensors and induce adaptation.^55^ ILEX is typically performed with pelvic stabilisation to effectively target the lumbar extensors while minimising gluteal and hamstring activation.^56^ Research shows that ILEX training leads to clinically meaningful improvements in strength, pain and disability in individuals with chronic LBP,^55 56^ with strength gains often preceding hypertrophy due to neural adaptations.^57^ These findings,^58^ supported by our pilot data,^35^ justify the use of high-load training in the proposed trial to promote both neural and morphological adaptations.^59^ ILEX training will be performed on the MedX Lumbar Extension Machine (MedX, Ocala, Florida). This dynamometer can be used to assess isometric lumbar extension muscular strength (torque) in a seated position and accommodate dynamic resistance training through a full 72° ROM. During weeks 1–4, participants will be performing three sets of 12 repetitions at a resistance load of 60% of maximum recorded functional torque (one-repetition maximum, 1RM), and repetitions will be performed until momentary failure to control for intensity of effort.^57 60^ From week 5 to week 10, three sets of 10 repetitions will be performed at 80% of 1RM, and from week 11 to week 16, three sets of eight repetitions will be performed at 80% of 1RM, always to momentary failure. Participants will be instructed to perform repetitions taking at least 2 s to complete the concentric phase, hold the position/contraction for 1 s in full extension and then take 4 s to complete the eccentric phase.^60 61^ The resistance load will be increased by 5%^60 61^ at the next session once the participant is able to complete the set number of repetitions before failure.

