
### Sample size calculation

The sample size calculation was performed to compare the improvement in disability (eg, changes in ODI scores) from baseline to 16 weeks between MC+ILEX and free-weight resistance training exercise groups. This calculation was conducted using PASS 2023 software for two-sample t-test based on effect size. The minimum required sample size is 90 (45 per group) to detect a standardised effect size of 0.60 (Cohen’s d effect size), with 80% statistical power at the significance level of 0.05 (two-sided test), assuming an equal variance within the low (LSIQ<9) and high (LSIQ≥9) instability strata.^21^ Cohen’s d effect size of 0.60 falls within the range considered as a medium effect.^100^ This effect size is a conservative choice for the sample size calculation, given that the estimated Cohen’s d is approximately 0.79 based on the disability improvement observed in the MC+ILEX group from our previous work^35^ (mean=9.7, SD=10) and the disability improvement reported by Welch *et al*^34^ for the free-weight resistance training exercise group (mean=17.5, SD=5). A total of 106 participants (53 per group) will be recruited to account for a 15% loss to follow-up.^35 101^

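### The mediation percentage (indirect over total effect) is set without conditions, although it is a proportion only when the ODI difference is clear and direct and indirect effects agree in sign

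*Protocol article*

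**What the plan says.** The Statistical analysis section of the protocol article plans a path analysis: group to change in multifidus composition (a), change in composition to change in ODI (b), and group to change in ODI (c). It then states: "The direct, indirect and total effects of treatment on the change in multifidus muscle composition and its 95% CI will be calculated", using a non-parametric bootstrap. As an addition, "the mediation percentage is defined as the ratio of the indirect effect to the total effect, thereby quantifying the size of the mediation effect". A separate sentence covers inference: "The significance of the mediation effect will be tested using bootstrap sampling (times=1000").

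Three other statements bear on how the ratio will behave:
- The contrast is between two active programmes: "group (MC+ILEX vs free-weight resistance training").
- The Introduction says that "the effect sizes for differences between exercise approaches remain modest".
- The Sample size calculation is built to "detect a standardised effect size of 0.60". It also gives planning improvements in disability of 9.7 (SD 10) for MC+ILEX and 17.5 (SD 5) for free weights.

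**The concern.** A ratio of indirect to total effect is a share of something only if the total effect is the sum of two parts with the same sign. If the parts oppose each other, the ratio falls below 0% or above 100%. If the total is near zero, the ratio can take any size. The plan computes it in all cases and says that it quantifies the size of mediation.

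The denominator is exposed in this trial because it is a difference between two exercise programmes, a kind of difference that the article itself calls modest. Its direction is also open. The planning figures favour free weights on disability by 17.5 − 9.7 = 7.8 points. On the other side, the MC+ILEX section says that "MC will be combined with ILEX exercise to maximise the stimulus and activation of the lumbar extensors and induce adaptation".

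At stake is the reading of secondary aim 1, a central mechanistic question of the trial. A large or negative percentage that comes from a small ODI difference could be taken as strong or reversed mediation. The primary analysis is not affected.

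**Working it through.** **The plan's own figure.** For d = 0.60, two-sided 5% and 80% power, the two-sample t-test needs 44.6 per arm. This gives 45 per arm and 90 in total (power 80.4%). Then 90 / 0.85 = 105.9, so 106. The stated sample size is reproduced. The article gives no mediation figure to reproduce.

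**Formula.** With paths a (group to mediator), b (mediator to outcome) and c′ (direct), the total effect is ab + c′ and the ratio is R = ab / (ab + c′). R lies between 0 and 1 exactly when ab and c′ have the same sign.

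**How firm is the denominator?** In SD units with 45 per arm, the standard error of the total effect is √(2/45) = 0.211.
- At d = 0.60 the total is 0.60 / 0.211 = 2.8 standard errors from zero, so the estimate has the wrong sign in about 0.2% of trials.
- At d = 0.30 it is 1.4 standard errors away, with the wrong sign in about 8%.
- At d = 0 the sign is a coin toss.

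**Simulation.** Inputs from the article: 90 evaluable, 1:1 allocation, design d = 0.60. Assumptions, since the article gives no values: mediator and outcome with unit within-arm SD, b = 0.3, and a as listed in SD units. A positive a means a mediator difference in the direction that raises the total effect. The estimate is R = â·b̂ / total, with 10,000 trials per row (last row 40,000).

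| Total d | a | R outside 0–100% | 95% range of R |
|---|---|---|---|
| 0.60 | 0.3 | 8.6% | −8% to 55% |
| 0.60 | 0.5 | 2.7% | 3% to 79% |
| 0.30 | 0.3 | 21% | −166% to 270% |
| 0.30 | 0.5 | 24% | −254% to 389% |
| 0 | 0.3 | 65% | −819% to 727% |
| 0 | 0.5 | 76% | −1176% to 1185% |
| 0.60 | 0 | 50% | −39% to 24% |
| 0.30 | 0 | 49% | −145% to 126% |
| 0.60 | −0.3 | 92% | −79% to 5% |
| 0.30 | −0.3 | 90% | −344% to 265% |
| −0.60 | 0.5 | 99% | −110% to −2% |

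With a = 0 and d = 0.60, half the values are negative, but they cluster around zero and would mislead less.

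**Range over the assumed paths.** With a = b = 0.5 the shares outside are 4% (d = 0.60), 39% (d = 0.30) and 90% (d = 0). With a weak path (a = 0.2, b = 0.1) they are 29%, 34% and 54%.

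**Does a significant total effect suffice as a condition?** With b = 0.3 and same-direction mediation, it lowers the share outside at d = 0.30 from 21–24% to about 1–3%. With a = 0, 36% (d = 0.30) and 46% (d = 0.60) remain outside. With a = −0.3, 88% and 91% remain. A same-sign condition is needed as well.

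**The case against.** **The percentage is only an addition.** This is correct. The direct, indirect and total effects with bootstrap CIs come first, and mediation is tested by bootstrap, not by the ratio. A reader might infer that the percentage is the plan's only measure of mediation size, and the text does not support that. What remains is that the percentage is the one quantity to which the text assigns that role. The effects themselves are described as effects on multifidus composition, which is the mediator, so no effect on ODI is clearly named as the size measure.

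**At the design value the ratio mostly behaves.** Also correct, for a same-direction path of moderate size. A reader might conclude that the ratio will often be out of range, or that it cannot quantify mediation at all. Neither follows: the frequency depends on the true total effect and mediator path, and the ratio is usable when the total is clear and the signs agree.

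**Opposite ordering of the arms is conjecture.** A reader might infer from the 7.8-point planning difference and the purpose of ILEX that MC+ILEX will do better on multifidus and worse on ODI. The document does not show this. It does not compare the arms on lumbar loading, and the mediator is fat fraction, not activation. The free-weight section also reports a significant fall in intramuscular fat in the study that it replicates, which is the source of the 17.5-point improvement. That fits same-sign mediation equally well. Opposite signs are a possibility only.

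**The simulation is simple.** It leaves out the planned baseline ODI and LSIQ terms, which would normally improve precision. The shares are therefore indicative.

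**Reporting rules belong in a statistical analysis plan.** This would hold if the article left the matter open. It fixes both the definition and its interpretation, so the stated rule can be judged.

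**Conclusion.** The point holds as a limited one. The mediation percentage is unconditional and unbounded. It can be uninterpretable unless the total effect on ODI change is clearly non-zero and the direct and indirect effects share a sign. With 45 per arm and b = 0.3, the risk is small at d = 0.60 with same-direction mediation (about 3–9% of trials outside 0–100%). It is material at d = 0.30 (about 21–24%) and large if the arms are equal on ODI (65–76%). About half fall outside when the arms do not differ on the mediator, and at least 90% when the paths oppose each other. These shares rest on assumed values of a and b and on a model without covariates. The need for conditions follows from the algebra and does not depend on those values. This is a cheap improvement to a secondary analysis.

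**What to change.** Replace the sentence on the mediation percentage. Name the indirect effect, in ODI points with its bootstrap 95% CI, as the measure of mediation size, and show it beside the direct and total effects on change in ODI. This also requires the preceding sentence to refer to effects on ODI change rather than on multifidus composition.

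Then either delete the percentage or keep it as a supplement. If kept, report it only when the 95% CI of the total effect excludes zero and the direct and indirect effects have the same sign, and always with its own bootstrap CI. The same-sign rule puts the point estimate within 0–100% by construction but does not make it precise, which is why the CI must go with it.

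The change costs a sentence or two of wording before data are seen, with no new data or analysis. The downside is that no percentage is available when the arms do not clearly differ on ODI. In the simulation the total effect was significant in about 81% of trials at d = 0.60 but only about 29% at d = 0.30, so at the smaller difference the percentage would usually be withheld.

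### The mediation test is fixed at 1000 bootstrap resamples, which is valid but leaves avoidable simulation noise when the p value lies near 0.05; 10,000 would remove most of it at almost no cost.

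*Protocol article*

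**What the plan says.** In the protocol article, Objectives, the first secondary aim is to "assess whether changes in multifidus muscle composition mediate improvements in disability". The Statistical analysis section answers it with a path model: group to change in multifidus composition, that change to change in ODI, and group to change in ODI. Instability stratum and baseline ODI enter as exogenous variables. For the direct, indirect and total effects, the estimate and "its 95% CI will be calculated based on non-parametric bootstrap". On the test it says: "The significance of the mediation effect will be tested using bootstrap sampling (times=1000".

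The resample count is attached to the significance test, and no separate count is given for the intervals. The section does not say whether significance means a tail share, an interval that excludes zero, or a p value from a bootstrap standard error. It gives no level for this test. The only stated level is in Sample size calculation, for the primary comparison: "with 80% statistical power at the significance level of 0.05 (two-sided test".

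**The concern.** A bootstrap p value is itself an estimate, because another seed on the same data gives another value. If the test is read from the 2.5% tails, 1000 resamples put about 1000 × 0.025 = 25 values in each tail, which is few for a threshold decision. Near 0.05, a rerun could change the significance statement for the mediation question, which the Introduction presents as a key open question. The trial was sized for the ODI comparison and not for the indirect effect, so nothing in the article suggests that the mediation p value will fall well away from 0.05. Unlike sampling error, this noise can be reduced without recruiting anyone.

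**Working it through.** **The plan's own figures.** The article states no Monte Carlo error, so the only figures to reproduce are the sample sizes. It says: "The minimum required sample size is 90 (45 per group) to detect a standardised effect size of 0.60". For a two-sample t-test with d = 0.60 and two-sided 0.05, the noncentral t gives power 0.795 at 44 per group and 0.804 at 45, so 45 per group (90) is confirmed. 90 / 0.85 = 105.9, rounded up to 106, as stated. The mediation model would therefore be fitted to about 90 completers.

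**Inputs and assumptions.**
- B = 1000 (Statistical analysis).
- Level 0.05, two-sided: stated for the sample size only, carried over here as an assumption.
- Percentile-type p value (twice the smaller tail share): an assumption, with an alternative form in step 2.
- The limiting p is the value that infinitely many resamples would give.

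**Step 1. Monte Carlo error at a limiting p of 0.05.** With q = p/2, SE(p) = 2 × √(q(1 − q)/B).
- B = 1000: 2 × √(0.025 × 0.975/1000) = 0.0099. The 95% range of single runs is 0.05 ± 1.96 × 0.0099, or 0.031 to 0.069.
- B = 10,000: 0.0031, range 0.044 to 0.056.

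**Step 2. The other form of test.** If z = estimate / bootstrap SE and p is taken from the normal distribution, the bootstrap SE has a relative error of about 1/√(2B). At z = 1.96 and B = 1000, SE(z) = 1.96/√2000 = 0.0438. Multiplying by 2φ(1.96) = 0.1169 gives SE(p) of about 0.005, half the percentile figure.

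**Step 3. Confidence limits.** For a roughly normal bootstrap distribution, the simulation error of one 95% limit is √(0.025 × 0.975/B)/φ(1.96), in units of the effect's standard error. This is 0.084 at B = 1000 and 0.027 at B = 10,000. Squared, 0.084² = 0.007, so the noise adds about 0.7% to the sampling variance.

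**Step 4. Chance that one run falls on the wrong side of 0.05** (exact binomial tail, percentile form).

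| Limiting p | B = 1000 | B = 10,000 |
|---|---|---|
| 0.03 | 1% | below 0.1% |
| 0.04 | 15% | below 0.1% |
| 0.045 | 32% | 5% |
| 0.055 | 29% | 6% |
| 0.06 | 15% | 0.1% |
| 0.07 | 3% | below 0.1% |

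At exactly 0.05, either count lands on each side about half the time.

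**Step 5. Averaged over the p values that might arise.** This uses an assumed normal-theory distribution of the limiting p, with the percentile form.

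| Assumed situation | B = 1000 | B = 10,000 |
|---|---|---|
| p uniform | 0.8% | 0.25% |
| about 50% power | 2.7% | 0.85% |
| about 80% power | 1.9% | 0.6% |

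**Step 6. Simulation.** Path models of the plan's form were simulated with n = 90 and assumed effects, and two borderline datasets were each rerun over 40 seeds at B = 1000. In the first (p = 0.045 at 10,000 resamples), p ran from 0.024 to 0.062 and 65% of runs fell below 0.05. In the second (p = 0.054), p ran from 0.034 to 0.074 and 32.5% fell below 0.05. This agrees with step 4.

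**The case against.** The strongest reply is that nothing here is an error. One thousand resamples gives a valid test and does not bias the indirect effect, and the noise in a confidence limit is under 1% of the sampling variance. The alarming figures apply only close to 0.05, and at exactly 0.05 no finite count settles the verdict. The average chance of a changed verdict is at most about 3%, so the gain from 10,000 is at most about 2 percentage points on one secondary analysis. The plan also reports effects with intervals and a mediation percentage, so a result at 0.04 and one at 0.06 would look nearly the same. All of this stands, and it is why the point ranks low.

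It also stands that the percentile form and the 0.05 level are assumptions. A reader might infer that the decision is read from 25 values per tail, but the article does not say so, and a test based on a bootstrap standard error would halve the noise. A reader might also take the lack of a stated seed, or of a statement that test and intervals share resamples, as a defect. Those are details that an analysis plan not shown may hold. A seed makes a result repeatable but does not reduce Monte Carlo error, and nothing in the text says that the intervals and the test use different resamples.

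What does not follow is that the count should stay. It is a number that the article itself fixes, and the noise it leaves is avoidable.

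**Conclusion.** The point holds as an optional gain in precision, with low materiality. At 1000 resamples the verdict on mediation depends noticeably on the seed only if the limiting p lies between about 0.03 and 0.07. Within that band the dependence can be substantial, about 30% at 0.045 or 0.055. Across all p values it is about 1% to 3%, against less than 1% at 10,000. These figures rest on a two-sided percentile-type test at 0.05 and, for the averages, on an assumed distribution of p.

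A reader might go further and conclude that the mediation test is invalid, its estimate biased, or its result arbitrary. The documents do not support that, and the primary ODI result is not involved.

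**What to change.** In the mediation paragraph of Statistical analysis, replace 1000 with 10,000 resamples and state that the count applies to both the significance test and the confidence intervals of the direct, indirect and total effects. This narrows the zone in which the seed matters but does not remove it.

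The cost is one number in the text and a little computing time. The model is small, with about 90 completers. The plan also calls for multiple imputation, with an unstated number of imputations, and repeating the bootstrap in each imputed dataset should still be a modest load. Recruitment, data collection and the effects being estimated are unchanged.
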